**4.3 Quality of Life** Quality of life (QOL) is defined by the World Health Organization as 'individuals' perception of their position in life in the context of the culture and value systems in which they live and in relation to their goals, expectations, standards, and concerns (Martin & Amin, 2017).

5. Standard Operating Procedures to address registry operations and analysis activities, such as patient recruitment, data collection, data management, data analysis, reporting for adverse events, and change management.

**5.1 Recruitment** **5.1.1 Recruit group** Group selection criteria# **Exclusion criteria:** classes participating in exercise Four classes were randomly selected by the university for the elderly, among which three classes were the brisk walking group, the Taichi Chuan group, the combination of Tai chi chuan and the brisk walking group, and the other one was the control group.

5.1.2 Screening participants The researcher selects the participants who meet the criteria by asking and asking participants to fill out the PAR-Q questionnaire.

The inclusion and exclusion criteria to screen and then check by the doctor. 5.2 Data collection I.Data collection will start after obtaining the ethical approval, and completed the initial 2-week pilot test.

II.Prior to data collection, the potential participants will be approached and screen for illegibility. Then, they will randomly be assigned into 4 groups; 3 experimental groups (Wk, TCC, TCC+ BW) and 1 control group by stratified sampling.

Cross groups contamination will be control by only selecting 2 clinics in one district. In total 4 districts will be randomly selected. Each district will be randomly assigned to either BW, TCC, TCC+ BW, or a control group. Besides, III.the participants in this study will also be advised not to share any information about their exercise content, time, and other information with their friends and peers.

IV.Four qualified instructors and 4 assistance instructors will be appointed to assist the 4 intervention groups. These instructors will be responsible for monitoring the intervention for the group assign to them. Twenty enumerators that hold a Bachelor's Degree in PE will be appointed to monitor and assist the subjects in each group.

V.All participants are required to accept the intervention at the same time, for example, it is necessary to specify the morning or afternoon of each intervention.

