VI.Each experimental group selects 2 people to supervise and remind participants of their exercise status.

VII.1 person as a walking instructor with a national second-level sports social instructor qualification certificate, 1 person as a Tai Chi Chuan skill instructor with a third-level or higher qualification certificate for Tai Chi Chuan.

VIII.Participants in each group established a contact group and were reminded before each exercise. After the exercise, they were required to record a detailed exercise log, such as exercise time and exercise content.

IX.The process of instrument testing: Before the start of data collection, all instruments and documents required for testing will be checked to ensure the validity of the instrument during the test.

X.The test environment, test instruments, and test personnel are consistent. Test each test item 3 times, take the middle value.

XI.The data after the test are all checked and processed by two researchers. 5.3 Change Management A detailed manual of the process: If the international and reference standards change during the intervention, a detailed manual containing all registry strategies, processes, and protocols, as well as a complete data dictionary listing all data elements and their definitions, will be updated regularly. This is for researchers Data collection is crucial.

Infrastructure for continuous training: personnel changes are a common problem. Specific procedures and training infrastructure should be provided at all times to cope with any unexpected changes and replacements of registered personnel or providers who regularly enter data into the record office.

The method of notifying the change: through the mobile phone group, so that the participants can report the relevant data during the exercise to the recorder in time.

6. Sample size assessment

This was based on a four-group design and the assumption of detecting a moderate effect size (partial  $\eta^2 = 0.06$ ) for a given parameter, a moderate correlation of  $r = 0.5$  almost 1 repeated measures, a level of  $\alpha = 0.05$ , and power ( $1 - \beta$ ) of 0.8 (Timmons et al., 2018). This study will be conducted as a cluster-randomized trial (CRCT) with 4 groups and 20 people per group. The ICC value of 0.01 is used in the calculation of the design effect in this study (Killip et al., 2004). As such the design effect was calculated as below:

$$DE = 1 + \rho(m-1) \quad DE = 1 + 0.01(20-1) = 1.19$$

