$$ESS = \text{effective sample size} = 80 * 1.19 = 96 \text{ (24 subjects per each group)}$$

According to the literature found in the highly relevant literature of this study, the final dropout rate was 5.75% (Guo LX., 2011). Considering this matter, the final sample size will be considered as 26 subjects per group and the total sample size of the study will be  $n = 104$ .

7. Plan for missing data to address situations where variables are reported as missing, unavailable, non-reported, uninterpretable, or considered missing because of data inconsistency or out-of-range results.
8. Statistical analysis plan The main methods of data collection in this study were statistical analysis and descriptive analysis.

Data will be analyzed using SPSS software (version 27, IBM Company, Chicago, IL, USA). Statistical significance will be reported at the 0.05 level. The data analysis will be preceded by data cleaning and assumption testing. Descriptive statistics will be used for all variables. Descriptive statistics will be reported as means and standard deviations (SD) or medians and interquartile range (IQR) for continuous variables (according to their distribution) and frequency and percentage for categorical variables. Two Way repeated measure ANOVA/ANCOVA or Generalized Estimating Equation (GEE) model for evaluation of the effectiveness of intervention programs on dependent variables will be used. Before the statistical analysis, assumptions underlying each statistical test will be checked and appropriate measures were taken when assumptions are violated.

[figure not shown] **NOTE :** Detailed Description should have no more than 12000 characters.

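### The unit of allocation is described in incompatible ways, and the cluster design used for the sample size has one cluster per arm, so exercise type cannot be separated from class, district or instructor

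*Protocol*

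**What the plan says.** All of the relevant text is in the protocol's Detailed Description.

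- **Item 5.1.1 (Recruit group), by class:** "Four classes were randomly selected by the university for the elderly, among which three classes were the brisk walking group, the Taichi Chuan group". The sentence goes on to give the combination arm and the control arm one class each.
- **Item 5.2, II, wording that reads as individual assignment after screening:** "Then, they will randomly be assigned into 4 groups; 3 experimental groups (Wk, TCC, TCC+ BW) and 1 control group by stratified sampling".
- **Item 5.2, directly after, by district:** to limit contamination, two clinics are taken per district, and four districts are chosen at random. The rule for reaching an arm is then "Each district will be randomly assigned to either BW, TCC, TCC+ BW, or a control group".
- **Item 6 (Sample size assessment):** "This study will be conducted as a cluster-randomized trial (CRCT) with 4 groups and 20 people per group". The ICC is 0.01 and the design effect is 1 + 0.01(20 - 1) = 1.19. The total goes from 80 to 96 (24 per group), and to 104 (26 per group) after dropout of 5.75%.
- **Item 8 (Statistical analysis plan):** "Two Way repeated measure ANOVA/ANCOVA or Generalized Estimating Equation (GEE) model for evaluation of the effectiveness of intervention programs", with significance at the 0.05 level.

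The Study Design section records the allocation as randomized and the model as factorial, with 100 actually enrolled. It does not name the unit.

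**The concern.** The unit of allocation decides what the trial can show, and it belongs in the protocol. A class of a university for the elderly and a district with two clinics are different units. Neither is an individually assigned participant.

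The sample size adopts the cluster version with a cluster as large as the arm. The class and district versions also give four units for four arms. An arm difference could then come from the exercise, from the class or district, or from the instructors, whom item 5.2, IV makes responsible for the group assigned to them. The data cannot tell these apart.

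The design effect suggests that clustering has been dealt with. It has not: a design effect adjusts the number of people when clusters are replicated within arms, and here they are not. Calling the trial randomized would then claim a protection that four units spread over four arms do not give.

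**Working it through.** **1. The plan's own figures.** Inputs from item 6: starting total 80 (taken as given), ICC 0.01, m = 20, dropout 5.75%.

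- Design effect = 1 + 0.01 × (20 - 1) = 1.19.
- 80 × 1.19 = 95.2, rounded up to a multiple of four: 96, or 24 per group.
- 24 / (1 - 0.0575) = 25.5, rounded up to 26; 26 × 4 = 104.

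The chain from 80 to 104 reproduces, and its m is the number of people in an arm.

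**2. Replication.** Between-cluster error degrees of freedom = arms × (clusters per arm - 1) = 4 × (1 - 1) = 0. More people per cluster leave this at zero. The two clinics per district do not change it, because the district is what is assigned and m = 20 does not treat clinics as clusters. A cluster random effect, or a cluster-robust variance in a GEE, cannot be estimated when cluster and arm coincide.

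**3. Type I error if the cluster effect is present in the analysed quantity.** With one random cluster per arm and n people in it, the usual four-group F statistic under no exercise effect is distributed as s × F(3, 4(n - 1)), where

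s = (1 - ICC + n × ICC) / (1 - ICC).

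True type I error = P[F(3, 4(n - 1)) > critical value / s]. For a pairwise t test with 2(n - 1) degrees of freedom, the critical value is divided by √s. At n = 24 the 5% critical values are 2.704 for F(3, 92) and 2.013 for t(46).

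| ICC | s | 2.704 / s | Four-group test | 2.013 / √s | Pairwise test |
|---|---|---|---|---|---|
| 0.01 (protocol) | 1.242 | 2.176 | 9.6% | 1.806 | 7.7% |
| 0.02 (assumed) | 1.490 | 1.815 | 15.0% | 1.649 | 10.6% |
| 0.05 (assumed) | 2.263 | 1.195 | 31.6% | 1.338 | 18.7% |

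A simulation of 40,000 trials at ICC 0.01 also gave 9.6% for the four-group test. With the 100 enrolled spread equally (25 per arm, an assumption), the figure at ICC 0.01 is 9.8%.

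**4. The condition on these figures.** The table applies to a single-measurement comparison such as the post-test value, or to change if the ICC applies to change. In a simulation with 24 per arm, one cluster per arm, a within-person correlation of 0.5 and a cluster effect constant over time, the group-by-time test stayed at about 5% at both ICC 0.01 and ICC 0.05. Inflation of that test needs clusters that differ in how much they change. The protocol gives no figure for that.

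**The case against.** Several points on the other side have force.

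- **The planned test may not be inflated.** A reader might infer that the plan's tests run at 9.6% at the protocol's own ICC. The documents do not support this without a condition. The group-by-time term is the usual effectiveness test in a two-way repeated-measures ANOVA, and a constant class or district effect drops out of it. This stands, so the error rates are conditional. The confounding remains, because an arm's instructor, or local events during the 12 weeks, can produce differential change.
- **There may be two units rather than three.** The sentence that reads as individual assignment sits beside the district sentences and may loosely describe participants reaching their arm through their district. That is possible. Class against district is the firm contradiction.
- **The SAP may handle clustering.** Item 8 names only model families, so it would go too far to say that the analysis ignores the ICC. But no choice of model can estimate a between-cluster variance from one cluster per arm.
- **Differences between testers.** A reader might add these to the list of confounders. Item 5.2, X says that test environment, instruments and personnel are consistent, so the documents do not support it.
- **Individual randomisation would end the matter.** It would remove confounding by allocation. It would not remove clustering from delivery: instructors are attached to groups, and each group has its own contact group. The design effect would therefore not automatically become redundant.

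**Conclusion.** The point holds. The allocation descriptions cannot all be true. Under the class or district version, the declared cluster-randomized design has one cluster per arm and zero between-cluster degrees of freedom. Exercise type is then fully confounded with class or district and with the arm's instructors, and raising 80 to 96 does not address this.

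The error rates worked out above describe the inflation only if the ICC applies to the quantity tested. Values above 0.01 are assumptions, and the protocol does not give the ICC of change. If individuals were in fact randomised, the confounding by allocation goes, but the cluster-randomized label is then wrong. Text has to change in every case.

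**What to change.** State the one unit of allocation actually used and delete the other descriptions. Then:

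- **If classes or districts were allocated:** describe the trial as one cluster per arm. Limit the conclusion to a statement that the arms differed, and say that class, district and instructor effects are not separable from exercise type. Add a sensitivity analysis that divides F by (1 - ICC + n × ICC) / (1 - ICC), and multiplies standard errors by its square root, for ICC 0.01 to 0.05. This is not a repair, since the ICC is borrowed and this trial cannot estimate it. Use the full factor rather than the design effect alone: dividing F by 1 + ICC(n - 1) leaves the four-group error at 5.2% for ICC 0.01 and 5.9% for ICC 0.05 (n = 24).
- **If individuals were randomised:** delete the cluster-randomized label, adjust for the strata, and justify any retained design effect as an allowance for clustering from group delivery.

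The cost is protocol and SAP wording and a short extra table. Under the class or district version, intervals in the sensitivity analysis are wider and the causal claim is weaker. No new participants are needed.

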## Study Description

**Brief Summary:** Aging is a problem that exists in many countries in the world. China has a large population base and a large number of elderly people. Paying attention to the health of the elderly is a problem that the Chinese government and society have been paying attention to. In order to improve the physical fitness of the elderly, the government encourages the elderly to do more exercise. However, the elderly do not exercise usually, and the way of exercise is relatively simple, which cannot meet the needs of comprehensive improvement of the elderly's physical fitness. For example, endurance, strength, flexibility, and balance are the most important to the elderly's physical fitness. Tai Chi Chuan is very popular in China. 79.36% of people in China choose brisk walking as the basic exercise. These two exercises have no venue, equipment requirements, and relatively simple technical movements. They are more convenient for the elderly to implement, and according to the literature It is found that Tai Chi Chaun is very effective in improving the balance and flexibility of the elderly, while brisk walking is very effective in improving endurance, and both Tai Chi and brisk walking can improve the strength of the elderly. Therefore, the combination of Taijiquan and brisk walking in this study can meet the four exercise components of elderly people's comprehensive development of physical fitness, endurance, strength, flexibility, and balance, and through the literature, it is found that the effect of combined exercise is better than that of a single exercise. Therefore, this study is divided into 4 groups, Tai Chi Chuan group, brisk walking group, Tai Chi combination brisk walking group, and control group. The aim of this study is to evaluate the effectiveness of combine brisk walking and Tai Chi Chuan (BWTCC) on health-related physical fitness and selected health parameters among older Chinese women. The specific objectives of these studies are as follows:

1. To evaluate the effectiveness of brisk walking (BW), Tai Chi Chuan (TCC), and their combination (BWTCC) on health-related physical fitness (Cardiorespiratory fitness, Body composition, Flexibility, Muscular Strength, and Muscular endurance) among older Chinese women at pre-test, post-test and at three (3) months post-intervention.

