2. To evaluate the effectiveness of brisk walking (BW), Tai Chi Chuan (TCC), and their combination (BWTCC) on health parameters (Blood pressure, Resting heart rate, Balance, Height, and weight) among older Chinese women at pre-test, post-test and at three (3) months post-intervention.

3. To evaluate the effectiveness of brisk walking (BW), Tai Chi Chuan (TCC), and their combination BWTCC on QoL among older Chinese women at pre-test and post-test.

The following hypothesis # HO1: There are no significant differences among the three intervention groups (BW, TCC and BWTCC) and with the control group on health-related physical fitness (Cardiorespiratory fitness, Body composition, Flexibility, Muscular Strength, and Muscular endurance) among older Chinese women at pre-test and post-test.

HO2: There are no significant differences among the three intervention groups (BW, TCC and BWTCC) and with the control group on health parameters (Blood pressure, Resting heart rate, Balance) among older Chinese women at pre-test and post-test.

HO3: There are no significant differences among the three intervention groups (BW, TCC and BWTCC) and with the control group on QoL among older Chinese women at pre-test and post-test.

[figure not shown] **NOTE : Brief Summary should have no more than 2500 characters.**

Detailed Description:

1. Quality assurance plan that addresses data validation and registry procedures Each group of sites that submit data to researchers has two personnel responsible for the quality of these data. The site coordinator has learned and fully understood all the agreements, policies, procedures, and definitions in the intervention process before the formal intervention process. All personnel involved in measuring and collecting data must learn systematic knowledge before the formal intervention, so as to ensure that all data are valid and accurate.
2. Data checks to compare data entered into the registry against predefined rules for range or consistency with other data fields in the registry.

Errors in data entry, transfer, or transformation accuracy: These occur when data are entered into the registry inaccurately. Avoidance or detection of accuracy errors can be achieved through upfront data quality checks (such as ranges and data validation checks), reentering samples of data to assess for accuracy (with the percent of data to be sampled depending on the study purpose), and rigorous attention to data cleaning.

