The sit-up (or curl-up) is an abdominal endurance training exercise to strengthen, tighten and tone the abdominal muscles.

Technique: Squeeze your stomach, push your back flat and raise high enough for your hands to slide along your thighs to touch the tops of your knees. Don't pull with you neck or head and keep your lower back on the floor.

[Time Frame: 5 minutes]

8. Cardiorespiratory endurance measurement by Six minutes walking test

Six minutes walking test (6MWT) could be considered as a useful and reliable tool for the assessment and the follow-up of cardiorespiratory response.

Equipment required: measuring tape to mark out the track distances, stopwatch, chairs positioned for resting.

Procedure: The walking course is laid out in a 50 yard (45.72m) rectangular area (dimensions 45 x 5 yards), with cones placed at regular intervals to indicate distance walked. The aim of this test is to walk as quickly as possible for six minutes to cover as much ground as possible. Subjects are set their own pace (a preliminary trail is useful to practice pacing), and are able to stop for a rest if they desire.

[Time Frame: 6 minutes]

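### Eight primary outcomes, a single 0.05 level and no success rule: if any one result counts, the familywise error is up to 0.34 (independent outcomes), and about 0.26 to 0.32 at correlations of 0.5 to 0.2

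*Protocol*

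**What the plan says.** The Outcome Measures section numbers eight primary outcomes: waist circumference, sit-and-reach, back scratch, chair stand, arm curl, knee push-up, sit-up and, last, "8. Cardiorespiratory endurance measurement by Six minutes walking test". The secondary list starts at number 9. No primary outcome is ranked above another, and nothing says whether one positive result, several or all eight are needed.

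The Detailed Description, item 8 (statistical analysis plan), states "Statistical significance will be reported at the 0.05 level". It offers repeated-measures ANOVA/ANCOVA or GEE as the model. Item 6 (sample size) uses partial eta squared 0.06 for one unspecified parameter, correlation 0.5, alpha 0.05 and "power ( $1 - \beta$ ) of 0.8". Alpha is not divided across outcomes.

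The first null hypothesis in the Brief Summary reads "There are no significant differences among the three intervention groups (BW, TCC and BWTCC) and with the control group on health-related physical fitness", and then lists five fitness components. The aim is worded "The aim of this study is to evaluate the effectiveness of combine brisk walking and Tai Chi Chuan (BWTCC" and so on; it does not mention single exercises. A background sentence just before the aim says the literature finds combined exercise better than a single exercise. Study Design labels the model factorial.

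**The concern.** The first null hypothesis covers five fitness components, measured by eight primary tests: one for body composition, two each for flexibility, strength and muscular endurance, and one for cardiorespiratory fitness. The protocol does not say how eight results combine into one conclusion. With a single 0.05 level and no hierarchy, one significant result out of eight could be presented as a positive trial, and nothing in the text prevents it. The trial is open label, so choosing a lead outcome after results are known is a practical risk.

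The second issue is what a positive result would mean. The case for a combination arm in the Brief Summary is that it does better than one exercise, but no hypothesis isolates that comparison. A significant four-group result caused only by exercise against no exercise could be taken as support for the combination.

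**Working it through.** **The plan's own figures.** The protocol states no familywise error rate, so there is none to reproduce. The sample size starts from "4 groups and 20 people per group", that is 80. "The ICC value of 0.01 is used in the calculation of the design effect", so the design effect is 1 + 0.01 × 19 = 1.19 and 80 × 1.19 = 95.2, stated as 96 (24 per group). The protocol says "the final dropout rate was 5.75"%, so 24 / (1 - 0.0575) = 25.5, rounded up to 26 per group, 104 in total. These steps reproduce. The starting 80 did not follow from the stated inputs under any reading tried with two or three measurements; that is a separate matter. What counts here is that alpha enters once, at 0.05, for one parameter.

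**Inputs.** Number of primary outcomes: 8 (Outcome Measures). Level: 0.05 (Detailed Description, item 8). Groups: 4. Correlation among the outcomes: not given, so it is an assumption and a range is shown.

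**Independent outcomes, all nulls true, a claim on any one.**
Familywise error = 1 - (1 - 0.05)^8 = 1 - 0.663 = 0.337.

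**Correlated outcomes.** Simulation of eight equally correlated outcomes, four groups of 20, one four-group F test per outcome at 0.05, 20,000 replicates:

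| Assumed correlation | Familywise error |
|---|---|
| 0 | 0.332 |
| 0.2 | 0.319 |
| 0.3 | 0.300 |
| 0.5 | 0.267 |
| 0.7 | 0.205 |
| 0.8 | 0.167 |
| 0.9 | 0.124 |

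With 24 per group the values at correlations 0, 0.3 and 0.5 are 0.338, 0.304 and 0.263. The 0.332 and 0.338 at zero correlation agree with the exact 0.337 within simulation error.

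These figures let each test hold its nominal 5% and count one test per outcome. Clustering left out of the analysis, or separate tests by time point or by pair of groups, would raise them.

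**With correction.** Holm's first threshold is 0.05 / 8 = 0.00625. At that level for all eight, independence gives 1 - (1 - 0.00625)^8 = 0.049. Holm controls the familywise rate at 0.05 whatever the correlation.

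**What a four-group rejection shows.** Suppose the three exercise arms are identical and each is d = 0.8 SD better than control. For n per group, the noncentrality is 4n × (3/16) × d²:
- n = 20: 80 × 0.1875 × 0.64 = 9.60, rejection probability 0.72
- n = 24: 96 × 0.1875 × 0.64 = 11.52, rejection probability 0.805
- n = 26: 104 × 0.1875 × 0.64 = 12.48, rejection probability 0.84

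The test rejects in most such trials although the combination has no advantage over either exercise.

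**The case against.** **The 0.05 sentence does not exclude adjustment.** Adjusted p-values can also be judged against 0.05, and the adjustment method and post hoc contrasts are commonly left to an SAP, which is not shown here. This stands in part: the missing method alone would be weak ground. What the protocol does fix is eight co-equal primary outcomes, one level and a sample size at undivided alpha, with no rule for success. Those need settling in the outcome list itself.

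**One in three is not the error rate as such.** A reader might take 0.337 as the trial's false-positive risk. It needs independence, all nulls true and a claim on any one outcome, and the protocol states none of these. The measures come from the same women and several share a domain, so some correlation is likely. This objection stands, and the range belongs with the figure.

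**The hypothesis need not be omnibus.** Its wording can also be read as comparisons between the exercise arms plus each arm against control, and the protocol nowhere says that only a four-group test will be run. This stands. One can calculate about 66% (independent) to 54% (correlation 0.5) for three unadjusted contrasts of the combination on all eight outcomes. The protocol does not state that analysis, so these are not its error rate.

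**The aim is not combination against single exercise.** The aim and Objective 1 ask about effectiveness; only the background rationale claims an advantage over a single exercise. This stands, and limits the contrast issue to a secondary point.

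**Conclusion.** The concern holds in conditional form. Eight primary outcomes with one 0.05 level and no lead outcome, order or success rule leave the familywise error uncontrolled if any one result may carry the claim. With all nulls true and one four-group test per outcome, it is at most about 0.34 under non-negative correlation, about 0.26 to 0.32 at moderate correlations, and still more than twice nominal at 0.9. The correlations are assumptions.

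The contrast issue is secondary. A significant four-group test would not by itself support the advantage that the rationale suggests. The documents do not support the stronger inferences that only an omnibus test is planned, or that superiority over single exercise is the stated aim; an SAP could supply the contrasts.

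**What to change.** Before post-test data are analysed, choose one of two routes.

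1. Keep all eight as primary. Define one group-effect (group-by-time) p-value per outcome and apply Holm across the eight at familywise 0.05: smallest p against 0.00625, the next against 0.05 / 7, and so on.
2. Name one of the eight as primary and make the other seven secondary, recording and dating the change in the outcome list.

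For statements about particular arms, name five contrasts: combination minus brisk walking, combination minus Tai Chi, and each of the three exercise arms minus control. The comparisons with control are needed for Objective 1. Test them only for outcomes that pass the Holm step, with multiplicity adjustment within each outcome. This controls error within an outcome. If one 0.05 is wanted over all contrasts on all eight, run the within-outcome adjustment at 0.00625.

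**Cost.** Route 1 needs wording only and loses some power per outcome. The loss depends on how the stated effect size is read. At N = 80 with two measurements, moving from 0.05 to 0.00625 lowers power from 0.97 to 0.86 if the effect is a standard group-by-time interaction with correlation 0.5. It lowers power from 0.41 to 0.15 if partial eta squared is taken in the SPSS convention. Holm's later steps are less strict, so this is its worst case. Route 2 keeps the full 0.05 for one outcome but changes the registered outcome list of a trial that has already enrolled 100 women, so the change must be visible.
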